### Overview of economic evaluation

This protocol has been reported in line with the Consolidated Health Economic Evaluation Reporting Standards (CHEERS) checklist [28] (see Supplementary File 1: CHEERS Checklist).

The economic evaluation of the HEI trial is two-fold. First is to conduct a cost and cost-effectiveness analysis of the fund and contract dissemination strategy for the BHF adoption, the BHF Online Training Resources and Program Package relative to BHF adoption and implementation, and the BHF-LC implementation strategy for promoting BHF adoption, implementation fidelity, and sustainability for the duration of the trial (12 months). The second is to conduct a cost and cost-effectiveness analysis of the BHF intervention. The CEA will be conducted from an implementing community [29] and limited societal perspective (i.e., including only productivity loss of participants due to the participation in the BHF program). The perspective of implementing community would include costs of time spent on planning, training, recruitment, delivering, and post-session follow-up, resources used, communication with the research team and BHF participants, and opportunity costs of community facilitators. Moreover, we will include the time and costs of the research team for providing training, facilitation, and technical assistance. Costs associated with research administration, data collection, and trial outcome assessment will be excluded. All costs will be categorized as labor and non-labor costs (e.g., space, supplies, or information technology) and expressed as US $2022. The unit of analysis for the economic evaluation is the 7 communities consisting of approximately 21–28 community facilitators who will be provided with BHF Online Training Resources and Program Package with or without a LC implementation strategy to implement and deliver the BHF intervention. The time horizon of the within-trial CEA will be across a 15-month period of time (first 3 months for preparation, and later 12 months for BHF intervention), to incorporate sufficient time to complete the whole implementation process of one BHF cohort, initiating from preparation, training, recruitment, and program delivery to post-intervention follow-up. This differs from the primary clinical effectiveness time horizon of 6 months. Costs and benefits will not be discounted due to a short duration.

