### Cost measurement

#### Labor costs

##### Dissemination and implementation strategies

The cost estimation of D&I strategies is guidied by the activity-based costing and Proctor framework, which is similar to the modified time-driven activity-based costing (TDABC) proposed by Cidav and colleagues [30]. We further extend the activity-based costing approach of implementation strategies to include opportunity costs, which are often overlooked and are key elements when considering the perspective of small-scale stakeholders [29], incurred by individuals (in our case, community facilitators) who are the target of D&I strategies. As the costs of D&I strategies are typically labeled as either labor (from performing the implementation activities) or non-labor costs (derived from the invoice or administrative data), the labor costs in a D&I strategy will be calculated by multiplying the hourly wages of personnel (*actor*) who conduct activities (*action*) associated with a D&I strategy with the amount of times and frequencies (*dose* and *temporality*) spent on activities plus the opportunity costs incurred by the strategy recipients (*action target*) (Table 2). The costs per D&I strategy will be calcuated as: $${C}_i={S}_i+\sum_{j=1}^m{X}_{ij}$$, where *C*_*i*_ = costs per discrete D&I strategy *i*; *X*_ij_=costs associated with activity *j* assigned to a D&I strategy *i*; *j* = activity *j* associated with a D&I strategy *i*; *j* = 1, 2, 3, …, *m*; and *i* =1,2,3,...; and *S*_*i*_ = amount of non-labor costs assigned to implementation strategy *i*. We will use the national hourly wage rate, corresponding to the position identified, of each community facilitator, CAB members, and research team members for estimates of labor costs.

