Table 2 details the specification of each D&I strategy used in the HEI trial and the application of the specification for estimates of labor costs. For example, categorized by implementation activities, the actor in the fund and contract dissemination strategy includes research team members, CAB members, and a project coordinator. The hourly wage rate of each personnel involved in a specific activity can be easily derived from the the US Bureau of Labor Statistics [31]. The activities involved in this strategy including drafting the LOI and the full applications to be distributed to interested communities that may respond to the RFA, and reviewing the application materials, meetings to discuss the application and make a decision, and contacting the awardees. To obtain the total cost for each implementation activity, we will multiply the total time spent on each activity by each research team and CAB member and community facilitator by their corresponding hourly wage rate. Similar exercises will be applied to all other activities. The total labor cost of a discrete D&I strategy will be derived by summing up the total cost of each implementation activity associated with that discrete strategy. Similarly, we will calculate the total labor cost of the LC strategy and the BHF Online Training Resources and Program Package by summing up the costs associated with each activity specified (Table 2), applying the similar steps stated above.

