##### BHF program training, recruitment, and delivery

The cost of the BHF program is estimated by the following components—BHF online module training, participant recruitment, and BHF program delivery. We will use the similar costing approach proposed for D&I strategies to estimate the costs of BHF program training, recruitment, and delivery. The labor cost of the BHF program training, recruitment, and delivery will be estimated by the time spent on activities of training, participant recruitment, session preparation, delivery, and post-session follow-up and national hourly wage rates of the similar position of community facilitators who enacted the activities. In the limited societal perspective, we will take into account the opportunity cost of the families attended the intervention sessions and other use (e.g., individual consultation), using the average national average hourly wage rate [31], and the transportation costs, estimated by the time spent on transportation and standard mileage reimbursement [32]. Table 3 presents detailed cost specification of BHF program online training and delivery.

**Table 3 Tab3:** Labor activity specification of implementing BHF intervention in the HEI trial by the Proctor framework [24]

Intervention	Outcome	Action	Actor	Target	Temporality	Dose (frequency)	Dose (duration)^**a**^
BHF program training, recruitment, & delivery	**Effectiveness** -BMI *z*-scores at baseline, 6-, & 12-month (child) -Weight/BMI (lbs.) at baseline, 6-, & 12-month (parents)	**BHF program delivery** -Information meeting -12 core courses across 12 continuous weeks -3 relapse prevention refresh courses -6-month assessment -1 relapse prevention refresh course -12-month assessment	-BHF-LC -BHF-PO	Child and parents dyads	-Baseline -First 12 weeks -Every 3 weeks -at 6 months -between 6 months & 1 year -at 12 months	Minimum 32 contact hours	-1 h -2 h per sessions -1 h per course -1 h -2 h -1 h
		**BHF program online training** -Information meeting -12 core courses across 12 continuous weeks -3 relapse prevention refresh courses -6-month assessment -1 relapse prevention refresh course -12-month assessment	-BHF-LC -BHF-PO	Child and parents dyads	Date of the training sessions	18 modules	Duration of the training sessions
		Recruitment/meeting/consultation	Research team	BHF-LC BHF-PO	Date of the consultations	As needed	Duration of the consultations

*BHF* Building Healthy Families, *LC* learning collaborative, *PO* Package only, *BMI* body mass index

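### Base-case labor cost is hours times a national wage with no employer-paid benefits, so at a given wage it understates the cost of employed staff time

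*Protocol article*

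**What the plan says.** Three places in the protocol article fix the unit price of staff time.

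- Under Labor costs, Dissemination and implementation strategies, the cost of a strategy is a non-labor amount plus the sum of its activity costs: "We will use the national hourly wage rate, corresponding to the position identified, of each community facilitator, CAB members, and research team members".
- The same section names the source, "The hourly wage rate of each personnel involved in a specific activity can be easily derived from the the US Bureau of Labor Statistics", and gives the calculation: "we will multiply the total time spent on each activity by each research team and CAB member and community facilitator by their corresponding hourly wage". The only further labor term is the opportunity cost of those who receive the strategy.
- Under BHF program training, recruitment, and delivery, time is priced at "national hourly wage rates of the similar position of community facilitators who enacted the activities".

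On perspective, Overview of economic evaluation states: "The CEA will be conducted from an implementing community [29] and limited societal perspective". It also counts research-team time for training, facilitation and technical assistance, and the opportunity costs of facilitators.

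The list under Non-labor costs covers space, supplies, equipment and participant incentives. The one-way analysis under Sensitivity analysis varies the role and salary level of key personnel, in an open list. Neither mentions benefits.

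**The concern.** For an organization that employs staff, an hour of their time costs the wage plus what the employer pays on top of it. A costing from the implementing community's perspective should carry both. The stated rule carries only the wage and leaves no other place for benefits to enter. They are not in the activity terms or the non-labor term, and recipients' opportunity cost is not an employer benefit. The article gives a reason for leaving out computers, Internet and landline, but none for leaving out benefits.

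The salary-level analysis moves the wage around its base value. It leaves the base-case ratios wage-only, and the bootstrap resamples costs built in the same way.

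The reported ratios are at stake, since Data analysis compares them with thresholds from earlier research. So are the replication costs, which the scenario analyses are meant to provide for communities considering adoption.

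**Working it through.** The documents state no wage, benefit rate, labor share, cost or ratio, so there is no planned figure to reproduce. The check follows the stated formula and shows what a benefit load would do.

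**Inputs**
- Cost of a strategy = non-labor cost + sum of (hours x wage), from Dissemination and implementation strategies.
- f = benefits as a share of wage. Not in the documents; assumed 20% to 45%.
- L = share of the wage-only cost that is employed staff time. Not in the documents; assumed 50% to 100%. For an ICER, L is the share of the incremental cost. Family time in the limited societal perspective is not employer-paid and does not count toward L.

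**Size at a given wage**

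Loaded cost / wage-only cost = 1 + L x f. Understatement = 1 - 1/(1 + L x f).

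| f | L | Loaded / wage-only | Understatement |
|---|---|---|---|
| 20% | 50% | 1 + 0.5 x 0.20 = 1.100 | 9.1% |
| 20% | 100% | 1.200 | 16.7% |
| 30% | 50% | 1.150 | 13.0% |
| 30% | 100% | 1.300 | 23.1% |
| 45% | 50% | 1.225 | 18.4% |
| 45% | 100% | 1.450 | 31.0% |

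**Average ratios.** In Table 1, the fund-and-contract row and the package row for knowledge score and fidelity divide total cost by total outcome. A larger numerator over the same denominator gives a larger ratio, so wage-only pricing understates them at a given wage.

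**Incremental ratios.** The sign matters. Take illustrative values: incremental labor cost 100, incremental non-labor cost 20, incremental effect 2, f = 30%.
- Wage-only: (100 + 20)/2 = 60. Loaded: (130 + 20)/2 = 75. The ratio is understated.
- With effect -2: wage-only -60, loaded -75.
- With incremental labor cost -100 and effect 2: wage-only (-100 + 20)/2 = -40, loaded (-130 + 20)/2 = -55.

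In the last two cases the ratio moves the other way, so it cannot be called understated. In the Table 1 rows for LC-driven fidelity and for maintenance, the package-only cost is none. The incremental cost is then the LC cost alone and positive, and the condition reduces to a positive effect difference.

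**Wage level.** The plan uses national wages. They would fully offset the missing benefits if local wage x (1 + f) were no more than the national wage, that is, local/national at or below 1/(1 + f). This is 1/1.20 = 83% at f = 20%, 77% at f = 30%, and 1/1.45 = 69% at f = 45%. The documents do not say where local pay stands.

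**The case against.** The strongest objection is that the consequence can easily be drawn too widely. A reader might infer that every ICER and ACER understates what the community pays for staff. The documents do not support that, for three reasons.

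- The sign condition above: with four communities against three, a zero or negative effect difference is possible.
- Table 2 gives most LC and fund-and-contract actions to the research team, the advisory board or the project coordinator, and no section shows the community paying for that time.
- National wages may lie above local pay in rural Nebraska, which would offset part or all of the omission.

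These points stand. They limit the claim to employed staff time at a given wage.

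A reader might also infer that nearly all strategy cost is labor. Table 2 lists labor by design, and the cost formula has a separate non-labor term, so the labor share is unknown. That the ratios would look better against any threshold cannot be checked either. The threshold source is not shown, and it may itself use wage-only costs.

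Two further objections carry less weight. An upward salary range in the one-way analysis has the same arithmetic effect as a benefit load, but no range is stated and the base case does not change. Benefits might also be thought a detail that a condensed article leaves to a fuller plan. Here, however, the article states the pricing rule, and a later benefit load would depart from it. The limitations section says that the pilot does not address decision makers' use of the results, yet replication costs for adopting communities remain a planned output.

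**Conclusion.** The point holds in limited form. Followed as written, the rule gives a base-case cost of employed staff time below the employer's cost at the same wage, which does not fit the implementing-community perspective. It lowers the average ratios, and the incremental ratios whose incremental labor cost and effect are both positive.

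The range of about 9-31% rests wholly on the assumed benefit rate and labor share, and neither is in the documents. It measures the gap at a given wage. The net difference from actual local pay is unknown in size and in direction.

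**What to change.** In the two labor-cost sections, price employed staff hours in the base case at wage x (1 + a stated benefit rate), or at total compensation. Set the rate by group: facilitators, research team, and advisory board members where they are employed. A single rate for all would overlook that their employers may differ or that some may be unpaid, and the article does not state their employment status. Leave family time at the wage.

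Report the wage-only result as a sensitivity analysis, which also allows a like-for-like comparison if the threshold source used wage-only costs. Add the benefit rate to the one-way deterministic analysis and its tornado diagram.

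The cost is one more assumed input for each employed group, and costs and ratios that will generally look less favorable. No new data collection is needed for the hours.

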##### BHF program training, recruitment, and delivery

The cost of the BHF program is estimated by the following components—BHF online module training, participant recruitment, and BHF program delivery. We will use the similar costing approach proposed for D&I strategies to estimate the costs of BHF program training, recruitment, and delivery. The labor cost of the BHF program training, recruitment, and delivery will be estimated by the time spent on activities of training, participant recruitment, session preparation, delivery, and post-session follow-up and national hourly wage rates of the similar position of community facilitators who enacted the activities. In the limited societal perspective, we will take into account the opportunity cost of the families attended the intervention sessions and other use (e.g., individual consultation), using the average national average hourly wage rate [31], and the transportation costs, estimated by the time spent on transportation and standard mileage reimbursement [32]. Table 3 presents detailed cost specification of BHF program online training and delivery.

**Table 3 Tab3:** Labor activity specification of implementing BHF intervention in the HEI trial by the Proctor framework [24]

Intervention	Outcome	Action	Actor	Target	Temporality	Dose (frequency)	Dose (duration)^**a**^
BHF program training, recruitment, & delivery	**Effectiveness** -BMI *z*-scores at baseline, 6-, & 12-month (child) -Weight/BMI (lbs.) at baseline, 6-, & 12-month (parents)	**BHF program delivery** -Information meeting -12 core courses across 12 continuous weeks -3 relapse prevention refresh courses -6-month assessment -1 relapse prevention refresh course -12-month assessment	-BHF-LC -BHF-PO	Child and parents dyads	-Baseline -First 12 weeks -Every 3 weeks -at 6 months -between 6 months & 1 year -at 12 months	Minimum 32 contact hours	-1 h -2 h per sessions -1 h per course -1 h -2 h -1 h
		**BHF program online training** -Information meeting -12 core courses across 12 continuous weeks -3 relapse prevention refresh courses -6-month assessment -1 relapse prevention refresh course -12-month assessment	-BHF-LC -BHF-PO	Child and parents dyads	Date of the training sessions	18 modules	Duration of the training sessions
		Recruitment/meeting/consultation	Research team	BHF-LC BHF-PO	Date of the consultations	As needed	Duration of the consultations

*BHF* Building Healthy Families, *LC* learning collaborative, *PO* Package only, *BMI* body mass index

^a^Preparation time and travel time (if any), and post-session follow-up (e.g., summary note) are also included

##### Non-labor costs

Non-labor costs include gym and classroom space, scales, diet books, printouts, handouts, educational supplies, equipment, and financial incentives provided for BHF participants and will be collected based on actual amounts spent and tracked from receipts and paid invoices. Costs of computers, Internet, and landline will not be included given that they are provided to community facilitators to conduct their daily tasks. To supplement the cost estimate of D&I strategies, we will also obtain cost information during the exit interview of community facilitators, as suggested by the literature [14].

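### Non-labor items are valued at what was paid, so delivery space used without payment enters at $0, and the arm difference in two ICERs can reflect who paid rent

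*Protocol article*

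**What the plan says.** The Non-labor costs section names the items: "Non-labor costs include gym and classroom space, scales, diet books, printouts, handouts, educational supplies, equipment, and financial incentives" for participants. It then gives the valuation rule: they "will be collected based on actual amounts spent and tracked from receipts and paid invoices". Computers, Internet and landline are left out because facilitators already have them for daily work; space is kept in.

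Two other sources of cost data are named. The same section adds: "To supplement the cost estimate of D&I strategies, we will also obtain cost information during the exit interview of community facilitators". The section on dissemination and implementation (D&I) strategies describes "non-labor costs (derived from the invoice or administrative data".

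The perspective, in Overview of economic evaluation, is that of the implementing community and includes "resources used, communication with the research team and BHF participants, and opportunity costs of community facilitators". The labor section says the method is extended to "include opportunity costs, which are often overlooked and are key elements when considering the perspective of small-scale stakeholders". Labor is priced at a standard rate: "We will use the national hourly wage rate, corresponding to the position identified". The section on BHF program training, recruitment and delivery prices family time at a national average wage and family travel with a standard mileage rate.

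**The concern.** Labor, family time and travel are costed as a quantity multiplied by a standard price, so two communities that use the same amount get the same cost. Non-labor items are costed at what each community happened to pay. A gym used for the same sessions costs the rent in one community and nothing in another, although the resource used is identical.

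Program delivery cost enters both arms in two rows of Table 1: the Effectiveness ICER and the ICER per additional cohort initiated. With only seven communities, one site's rental arrangement is a quarter of the LC mean or a third of the package-only mean. An incremental cost that should describe the learning collaborative would then partly describe local rental arrangements.

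The planned uncertainty analyses would not remove this. The bootstrap resamples the recorded costs, and a proportional one-way variation around a recorded $0 stays at $0.

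**Working it through.** **Inputs from the article**
- Communities: 4 BHF-LC and 3 BHF-PO (Eligibility, recruitment, and allocation).
- Contact time: at least 32 hours per cohort (Evidence-based pediatric weight management intervention).
- Horizon: 15 months, set to cover one cohort from preparation to follow-up (Overview of economic evaluation).

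**Assumptions, not in the article**
- Price of space: $20-60 per room-hour.
- Rooms in use at once: one or two.
- Costs compared as means per community. The article does not say whether C_LC and C_PO are means or totals.

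**Step 1: reproduce the 32 hours.**
- Program description: 12 × 2 h + 4 × 1 h + 2 h + 2 × 1 h = 32 h (12 weeks of refreshers, one every 3 weeks, gives 4).
- Table 3: 1 + 12 × 2 + 3 × 1 + 1 + 2 + 1 = 32 h.

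Both agree with the stated figure.

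**Step 2: space cost of one cohort.** Hours × rooms × price:
- low: 32 × 1 × $20 = $640
- high: 32 × 2 × $60 = $3,840

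Under the stated rule a community contributes this amount if it paid and $0 if it did not.

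**Step 3: effect on the arm difference.** With c the space cost per cohort, i of the 4 LC sites paying and j of the 3 package-only sites paying, the space part of the mean difference is c × (i/4 − j/3).
- All pay (i = 4, j = 3): $0.
- One package-only site unpaid (i = 4, j = 2): c × (1 − 2/3) = c/3, that is $640/3 = $213 to $3,840/3 = $1,280. The LC looks dearer.
- One LC site unpaid (i = 3, j = 3): c × (3/4 − 1) = −c/4, that is −$160 to −$960. The LC looks cheaper.
- Extremes (all of one arm pay, none of the other): ±c, that is ±$640 to ±$3,840.

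**Step 4: how easily the arms differ.** Suppose, as an illustration, that each site pays with probability 0.5 independently. There are 2^7 = 128 equally likely patterns. The paying shares are equal only when all seven pay or none does, so they differ with probability 1 − 2/128 = 0.98. They differ by at least 50 percentage points in 28 of the 128 patterns, or 0.22.

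**Step 5: with a common price.** Every site contributes c whether or not it paid, so at equal session hours the space part of the difference is $0. If one arm really uses more room-hours, that real difference is kept.

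**The case against.** - **Lent space is an inference.** This stands. No section says that any community has free space, and the call for letters of intent advertises funding, so paid space is equally compatible with the text. The point concerns what the rule does if space is unpaid. That is plausible, because the strategy seeks communities with strong cross-organization partnerships and the materials are adapted to local school and clinical partners.
- **Receipts are not the only source.** A reader might infer that they are, but the article also names administrative data, exit interviews and research team field notes, and says program costing follows a similar approach to that for D&I strategies. These other sources are tied to D&I strategies, however, and none is said to price unpaid delivery space.
- **Actual expenditure is a recognizable convention.** The opportunity costs named under the community perspective are those of facilitators, and existing computers and telephones are deliberately not charged. This has some force. But space is listed as a cost rather than excluded with the computers, and the perspective speaks of resources used.
- **Replication cost has its own scenario analyses.** This stands. A reader might infer that replication cost must be understated for a community that rents. The scenarios could price space, and their inputs are not listed, so the article does not show this.
- **Not every ratio is affected.** This stands. The Reach row lists training, consultation and recruitment costs, and the Implementation and Maintenance ICERs use LC cost alone. Delivery space does not enter those rows.

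**Conclusion.** The point holds in a limited form and should be acted on. The stated rule gives unpaid space and other unpaid non-labor items a value of $0, which is inconsistent with the article's resources-used perspective and with its standard prices for labor, family time and travel. The consequence is confined to the Effectiveness and cohort-adoption ICERs and can go in either direction.

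For one cohort per community, one unpaid package-only site raises the mean incremental cost by about $213-1,280 per community. This rests on the assumed $20-60 per room-hour and one or two rooms. Doubling it for the two cohorts per community in the enrollment goal would be tempting, but the economic horizon is built around one cohort.

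The article gives no rent, LC cost or program total, so whether the shift is large relative to an ICER cannot be judged from it.

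**What to change.** In Non-labor costs, value space and other unpaid in-kind items as quantity used × one common unit price with a stated source, in all seven communities, whether or not an invoice exists. Record room-hours per session at each site. The data collection section describes time logs and participant check-in sheets but does not say that either records rooms, so this is a small addition to the session record.

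Report as-paid expenditure as a secondary budget view. Vary the unit price in the one-way sensitivity analysis and in the replication-cost scenarios.

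The cost is one unit-price assumption that needs a source, a small recording task for facilitators, and a somewhat higher reported program cost.
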